### Data Management

All hard copy and audio-recorded data will be kept confidential and stored in a locked filing cabinet in the research group office and in softcopy in a password protected database according to ethical storage and disposal of data as stated in the NHMRC guidelines. Data will be only accessible to the chief investigator research officer, project manager, and statistician. The research team will monitor the integrity of the trial data. All participant data will be entered into an appropriate database such as Redcap (https://projectredcap.org/) or the Statistical Package for Social Sciences (SPSS) package and screened to detect any errors. A range of checks will be undertaken prior to data analysis.

The project manager will be employed to oversee the project and to manage the project data from each of the three states, including data cleaning and data merging.

### Statistical Methods

#### Data Analysis Plan

##### Quantitative Analysis

###### Primary Analyses

We will use all data along with the original designated group allocation and an intention to treat approach as the primary analytic framework. Descriptive data on both groups will be reported including demographics, stratification variables, baseline measures, and number of times intervention was accessed. Descriptive statistics will be used to summarize the characteristics of all participants including carers and family members. Deterioration of the primary outcome measure in individuals due to increasing dementia severity/aging and occurring over the 2-year data collection period will be explored using multivariate analyses (including factors: intervention status, age, and gender). If the dementia severity/aging factor is found to be significant, it will be included in the main models described below.

A linear mixed effects model will be used to compare the intervention and usual care periods for continuous outcomes and generalized linear mixed effects model for binary outcomes. The model will include intervention status and time as fixed effects and cluster site and individuals as random effects. Where appropriate, cluster and individual factors strongly correlated with the outcome will also be included as fixed effects in the model. These may include the stratification variables, e.g., socioeconomic status of area. The estimated intervention effect will be reported as the mean outcome difference for continuous outcomes and odds ratio for binary outcomes between intervention and control periods, assuming a constant treatment effect over time. The estimated intervention effects will be reported with 95% CIs and *p*-values. The analysis will investigate an interaction effect between intervention and time.

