## Methods: Assignment of Interventions (For Controlled Trials)

### Randomization

Clusters are community health centers participating in the study. Randomization of clusters to an intervention year (1 or 2) will be done using a minimization routine balancing numbers in groups as randomization proceeds (16). To guard against confounding by major differences in clusters, randomization will be stratified by state (Victoria, New South Wales, or Queensland), area (metropolitan or regional), and socioeconomic status of area that cluster is located within [defined by 1–3 versus 4–5 quintile of the area index of relative disadvantage (IRSD)].

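### The covariates of the primary model are left partly to the trial's own outcome data, one of them an undefined severity/aging factor that may be post-randomisation, and the allocation factors are optional

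*Protocol article*

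**What the plan says.** All of this stands in the Protocol article, mostly under Statistical Methods, Primary Analyses.

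- **Fixed core.** "The model will include intervention status and time as fixed effects and cluster site and individuals as random effects". The intention-to-treat approach and the effect measures (mean difference, odds ratio) are also fixed.
- **Entry rule 1, significance.** The subject is "Deterioration of the primary outcome measure in individuals due to increasing dementia severity/aging and occurring over the 2-year data collection period", which "will be explored using multivariate analyses (including factors: intervention status, age, and gender"). The rule then reads: "If the dementia severity/aging factor is found to be significant, it will be included in the main models described below".
- **Entry rule 2, correlation.** "Where appropriate, cluster and individual factors strongly correlated with the outcome will also be included as fixed effects in the model". No list of candidates and no threshold is given.
- **Allocation factors.** On membership of that second set: "These may include the stratification variables, e.g., socioeconomic status of area". Under Randomization, however, "randomization will be stratified by state (Victoria, New South Wales, or Queensland), area (metropolitan or regional), and socioeconomic status of area", the last split by IRSD quintile.

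Table 1 lists no instrument for dementia severity at any visit. The Missing Data section promises a detailed plan for secondary and sensitivity analyses; it does not mention the primary covariates.

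**The concern.** Three features of the stated rules cause difficulty.

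1. Under rule 1, the contents of the primary model depend on a test on the trial outcome, run with intervention status already in the exploratory model. A reader cannot say beforehand which model will yield the reported estimate, 95% CI and p-value.
2. The factor tested is described by what happens to the outcome after randomisation. A variable of that kind may itself be changed by the intervention, and conditioning on it would take out the part of the effect that runs through it.
3. Centres are allocated by minimisation on state, area and socioeconomic group, but the analysis is free to leave these out.

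At stake is whether the primary estimate is a single pre-specified quantity that measures the total effect of offering the programme.

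**Working it through.** **Step 1. What is open.** Intervention, time, centre and person terms are fixed. Open are the severity/aging factor (rule 1), the factors chosen under rule 2, and the three allocation factors. The covariate set floats; the model as a whole does not.

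**Step 2. What the severity/aging factor could be.** The article does not define it, so I take the possible readings in turn.

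- *Age at baseline.* A legitimate covariate that no treatment can alter. It needs no significance test and can be named now.
- *A time trend or current age.* Current age equals baseline age plus elapsed time. Time is already a fixed effect, so beyond baseline age this adds nothing.
- *Severity during follow-up, or the person's own outcome trajectory.* This is post-randomisation. With no severity instrument in Table 1, it would have to come from the outcome itself or from a measure the article does not name.

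Only the third reading biases the estimate. The wording on deterioration over two years permits it.

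**Step 3. Size under the third reading.** Let k be the share of the total effect acting through severity. The adjusted estimate is then (1 − k) × total effect. The article gives no k, so the values below are assumptions.

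| k (assumed) | Total 0.23 SD | Total 0.25 SD |
|---|---|---|
| 0 | 0.23 | 0.25 |
| 0.20 | 0.18 | 0.20 |
| 0.25 | 0.17 | 0.19 |
| 0.50 | 0.12 | 0.13 |
| 0.75 | 0.06 | 0.06 |

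A simplified two-group simulation (30 centres, 8 people each, true effect 0.25 SD) agrees. The adjusted estimates were 0.248, 0.186, 0.126 and 0.061 for k = 0, 0.25, 0.50 and 0.75. The unadjusted estimates stayed at 0.247 to 0.251.

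For scale, I reproduced the plan's detectable effect with a stepped-wedge variance: 15 centres per sequence, seven waves, ICC 0.05, power 0.80, two-sided 0.05 (assumed), no person effect, and Group B assumed still in control at 12 months. It is 0.224 SD with 10 per centre and 0.247 with 8, which brackets the stated 0.23 to 0.25. That calculation contains no covariates, so fixing them leaves it unchanged.

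**Step 4. Type I error.** In a simulation on 30 centre means with four candidate covariates, the error was 0.046 with all four fixed in advance. It was 0.097 when the most favourable of the 2⁴ = 16 covariate sets was reported. The second figure is a worst case for a different rule, because it selects on the treatment p-value. The article selects on association with the outcome, so the figure is not an estimate for this plan.

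**Step 5. Precision from the allocation factors.** Assume 8 people per centre, within-person correlation r = 0.7, total variance 1, and that the factors explain half of the ICC, so that the between-centre variance falls from 0.05 to 0.025. The covariance of centre-by-wave means is (τ² + σ²_person/m)J + (σ²_error/m)I, where J is the all-ones and I the identity matrix. The SE of the intervention term comes from generalised least squares with wave effects.

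| Contrast | SE, τ² = 0.05 | SE, τ² = 0.025 | Change |
|---|---|---|---|
| Year 1 only (four waves) | 0.0745 | 0.0732 to 0.0734 | 1.5% to 1.8% |
| Planned seven waves | 0.0532 | 0.0531 | about 0.3% |

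The year-1 range reflects two ways of handling the freed variance: person variance held at 0.65, or raised to 0.675 so that total variance stays at 1. The planned analysis uses seven waves, so the second row applies.

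**The case against.** The strongest reply is that little is really open. The core terms, the analysis framework and the effect measures are fixed. A full covariate list commonly sits in an analysis plan that is not shown. Rule 2 may mean factors known beforehand to be prognostic; its only example is a stratification variable. No severity measure is collected according to Table 1, so age or a time trend is at least as plausible a meaning as a mediator. Centre-level allocation factors are constant within a centre, and the random centre effect already carries between-centre variation. Leaving out balanced factors tends to make standard errors slightly too large, which is conservative.

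Most of this stands, and it rules out several stronger readings that a reader might infer:

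- *That the whole primary model is chosen from the data.* The text fixes its core.
- *That rule 2 selects on correlations observed in this trial.* It does not say so.
- *That the plan does adjust for a mediator and will dilute the effect.* This holds only under one reading of an undefined term, and its size rests wholly on an assumed k.
- *That the nominal 5% level and 95% CI are lost.* Nothing shown demonstrates inflation under selection on association with the outcome.
- *That omitting the allocation factors costs meaningful power.* It does not.

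The reply does not rescue rule 1. That rule is stated under Primary Analyses and cannot be read as prior knowledge. It is a selection rule the article sets out, not a detail left to another document. The one analysis plan the article announces is for secondary and sensitivity analyses. This does not prove that no primary plan exists, but nothing in the text defers the rule to one.

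**Conclusion.** The point holds for the covariate set of the primary model. As written, the trial's outcome data decide whether an undefined severity/aging factor enters, further factors enter by an unquantified criterion, and the factors used to allocate centres are optional. Two consequences follow. More than one primary estimate is possible. And if the factor is built from follow-up data, the estimate may no longer be the total effect: 0.23 SD could be reported as 0.18 to 0.12 SD for an assumed mediated share of 20% to 50%. If the factor is a time trend it is redundant; if it is baseline age it is harmless and can be fixed now. Precision is not an argument either way (about 0.3% of the SE with m = 8 and r = 0.7 assumed). The gain from correction is a primary model that is settled before outcome data are seen and protected from post-randomisation adjustment. It should be corrected; it does not call the design or sample size into question.

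**What to change.** Under Primary Analyses:

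1. Name the primary covariates in advance: state, area and IRSD group, plus baseline age and gender. Include them whatever their significance, alongside the fixed and random effects already specified.
2. Delete the significance rule for the severity/aging factor and the rule on factors strongly correlated with the outcome.
3. Keep any modelling of post-randomisation deterioration as exploratory, define the variable used, and state that it does not feed the primary estimate.

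The cost is analysis wording only. The three centre-level factors are needed for allocation, and age and gender are already used for the recruitment quotas and the imputation model. Because the article says that changes to analyses go to the ethics committees and the registry, the new wording should pass through that route before outcome data are analysed.

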### Sample Size

The study is powered to detect small–medium effects in the primary outcome measures of QOL-AD for people with dementia or cognitive impairment (0.23 effect size) and in the CES for carers (0.25 effect size).

The sample size required is 30 clusters with 10 participants/families in each to allow for an attrition of 20%. This is a total of 100 participant/families (50 in each group) in each of the 3 states, making a total sample size of 300. This will detect significant differences in caregiver’s and people with dementia or cognitive impairment’s quality of life between two groups at effect sizes of 0.23–0.25 (small–medium effects). Sample size calculations were completed using STATA statistical software stepped wedge: for clusters defined at the level of the community health center, power of 0.80, significance level set at 0.05, intraclass correlation coefficient (ICC) of 0.05, the number of steps (2), participant data collected at seven time points (baseline, 3, 6, 12, 15, 18, and 24 months), and primary outcome distributions as described in existing literature, i.e., QOL-AD scores between 15 and 60 and SD of 7 (6, 7, 14, 15) and CES scores between 0 and 100 and SD of 10 (8, 9).

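### The primary mixed model assumes within-centre correlation is constant over 24 months; if centre-level outcomes vary between visits, its standard errors are too small and type I error rises above 5%

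*Protocol article*

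**What the plan says.** The protocol article, under Primary Analyses, specifies a linear mixed model for continuous outcomes: "The model will include intervention status and time as fixed effects and cluster site and individuals as random effects". The effect is reported "assuming a constant treatment effect over time", with 95% CIs and p-values. The possible additions are stratification variables, other factors correlated with the outcome, a dementia severity/aging factor and an intervention-by-time interaction. All are fixed effects. No centre-by-visit term and no robust variance is named.

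The Sample Size section uses "power of 0.80, significance level set at 0.05, intraclass correlation coefficient (ICC) of 0.05", with "the number of steps (2), participant data collected at seven time points (baseline, 3, 6, 12, 15, 18, and 24 months". It gives one ICC and says nothing about whether within-centre correlation falls between visits.

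The Missing Data section defers a detailed plan only for secondary and sensitivity analyses. The primary model is therefore set out in this article.

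**The concern.** The same people are followed over seven visits, and every centre moves from control to intervention at one of two points. The effect is therefore estimated mostly from change within centres. A centre that shifts as a whole between visits, for example because local services change, moves all its participants together. With only centre and person intercepts, the model has nowhere to put that shared movement except the individual residual, where it counts as independent across the 8–10 people in the centre. The precision of the within-centre comparison is then overstated. The error runs in one direction: such variation can make the reported intervals too narrow but not too wide. Both primary outcomes are affected.

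**Working it through.** **Inputs from the article.** 30 centres, 15 per sequence; 10 people per centre, 8 after 20% attrition; the same people at visits 0, 3, 6, 12, 15, 18 and 24 months; ICC 0.05; alpha 0.05 (taken as two-sided); effect sizes 0.23 (QOL-AD) and 0.25 (CES). Exposure by visit: Group A 0,1,1,1,1,1,1; Group B 0,0,0,0,1,1,1.

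**Assumptions, because the article gives no figure.** Cluster autocorrelation (CAC) from 0.6 to 1. Within-person correlation r of 0.5–0.7, meaning the share of non-centre variance that persists between visits. Complete data with m = 8 or 10 per centre.

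**Set-up.** With total variance 1:

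- stable centre part c = ICC × CAC
- centre-by-visit part g = ICC × (1 − CAC)
- person part p = r(1 − ICC)
- residual e = (1 − r)(1 − ICC)

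The A-minus-B exposure difference by visit is 0,1,1,1,0,0,0, with mean 3/7. The within-centre sum of squares is S_w = 30 × ¼ × 12/7 = 12.857. The between-centre sum is S_b = 30 × (3/14)² = 1.378. The matching variances are v_w = g + e/m and v_b = c + p/m + v_w/7, and SE = 1/√(S_w/v_w + S_b/v_b).

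**Step 1: the plan's own figure.** Take a constant centre effect only (r = 0, CAC = 1) and m = 8. Then v_w = 0.95/8 = 0.1188, v_b = 0.05 + 0.1188/7 = 0.0670 and SE = 1/√(108.3 + 20.6) = 0.0881. The detectable effect is 2.80 × 0.0881 = 0.247, and power at 0.25 is 81.0%. This reproduces the stated size for CES. At 0.23, power is 74.2% with 8 per centre and 82.2% with 10, which is a separate matter. The stated size is thus consistent with a calculation that holds the centre effect constant over time.

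**Step 2: what the planned model reports when CAC is below 1.** It pools the centre-by-visit variation (180 − 6 − 1 = 173 degrees of freedom) with the person-level residual (180(m − 1) degrees of freedom):

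ẽ = [180(m − 1)e + 173·m·v_w] / [180(m − 1) + 173]

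Example with m = 8, r = 0.7, CAC = 0.8:

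- e = 0.285, g = 0.010, v_w = 0.0456, v_b = 0.1296
- ẽ = (359.1 + 63.1)/1433 = 0.2947, so the model uses ẽ/8 = 0.0368 where the true value is 0.0456
- weights: 12.857/0.0368 = 349.1 within and 1.378/0.1296 = 10.6 between, so 97% of the information is within-centre
- reported SE = 1/√359.7 = 0.0527
- true SE = √(349.1² × 0.0456/12.857 + 10.6² × 0.1296/1.378)/359.7 = 0.0585
- ratio 1.110, so type I error = 2Φ(−1.960/1.110) = 7.7%

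**Step 3: the range at ICC 0.05, m = 8–10, r = 0.5–0.7.**

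| CAC | Type I error, formula | Type I error, simulation (20,000 runs per setting) |
|---|---|---|
| 1.0 | 5.0% | 4.8–5.2% |
| 0.95 | 5.4–5.9% | 5.4–5.8% |
| 0.9 | 5.8–6.8% | 6.1–6.6% |
| 0.8 | 6.6–8.5% | 6.9–9.1% |
| 0.6 | 8.2–11.8% | 8.2–12.1% |

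**Step 4: with a centre-by-visit random effect.** In the same simulations type I error is 4.3–5.5%. With zero centre-by-visit variance it is 4.3–4.8%, slightly conservative.

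**Step 5: sensitivity.** With CAC 0.8 or higher, the planned model gives at most about 6.4% at ICC 0.02 and 5.7% at ICC 0.01. If the centre effect instead decays exponentially by a factor of 0.8 per 6 months (0.8⁴ = 0.41 at 24 months), the planned model reaches 12.5% and the model with the added term still gives 5.9–6.5%. If person-level correlation decays by 0.9 per 6 months and centre effects are stable, both models give about 6% (m = 8, r = 0.7).

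**Step 6: power after the change.** The worst case in the grid is m = 8, r = 0.5, CAC = 0.6: v_w = 0.0794, v_b = 0.1007, SE = 1/√(162.0 + 13.7) = 0.0755. Power at 0.23 is Φ(0.23/0.0755 − 1.96) = 0.86.

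**The case against.** A reader might infer that the planned standard errors are wrong and that the false-positive rate does exceed 5%. The document does not support that. The inflation needs centre-by-visit variance above zero, which the article neither gives nor excludes; if it is zero, the planned model holds 5%. The 12% figure is no expected value either, since it needs a CAC near 0.6 or strong decay, and nothing in the article points to those. This objection stands, and the point is conditional for that reason.

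The article also says random effects, not intercepts, and an article may leave covariance detail to a fuller plan. That carries some weight. But intercepts are the ordinary reading, and the deferred plan covers secondary and sensitivity analyses only.

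Some sources of drift should do little harm. Support workers are recruited by state and randomization is stratified by state, so state-level drift would be largely balanced between the groups. Drift specific to a centre remains possible: the Introduction reports that available services differ by state and by rural or metropolitan location.

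Finally, the added term is one choice among several. It does nothing for decay in person-level correlation, which is plausible in progressive dementia, and it only partly corrects strong exponential decay of the centre effect. That is a limit on the remedy. It does not make the constant-correlation assumption safer.

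**Conclusion.** The concern holds in conditional form. The primary model rests on constant within-centre correlation over 24 months. If that fails at the stated ICC, type I error moves from 5% to roughly 5.4–9% for CAC 0.95 to 0.8, and to about 12% at 0.6. In the formula results for CAC 0.95 to 0.8, the true standard error is about 2–14% larger than the reported one. A lower ICC shrinks the effect considerably. These sizes rest on assumed values for CAC, within-person correlation and analysed cluster size, and on complete data. This is a worthwhile improvement to a stated analysis choice. It is not a demonstrated error in the reported inference.

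**What to change.** Add a centre-by-visit random effect to the primary model for QOL-AD and CES. Fit by REML with a small-sample degrees-of-freedom correction (Satterthwaite or Kenward-Roger). Keep the planned model with two random effects as a sensitivity analysis, and make the choice before outcome data are seen by group.

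The change is one line of model specification. Confidence intervals become somewhat wider when centre effects drift, and at times slightly conservative when they do not. Under the assumptions above, power for 0.23 SD stays at about 0.86 or higher, so no change in sample size follows from this point. Because the term does not address decay in person-level correlation, a sensitivity analysis that allows correlation to fall with time between visits would be a sensible companion.

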### Missing Data

The analysis method chosen will use all available data. Every effort will be made to minimize missing outcome data at each wave, and reasons individuals are lost to follow-up will be recorded. A missing data analysis will seek to identify systematic patterns of missing data and identify instances where, despite the efforts of the research team, data may be missing not at random (MNAR). Whether or not data are identified as MNAR, for each primary outcome and other key variables with missing data, multiple imputation using multivariate regression with factors of age, gender, state, and time will produce 100 estimates for each missing item – supporting optimal statistical estimation. Sensitivity analyses will be conducted to assess the robustness of the missing data assumption made in the primary analysis. A detailed analysis plan will be developed for secondary and sensitivity analyses.

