**Figure 1 F1:**
[figure not shown]
**“Support for Life” stepped wedge cluster randomized control trial (SWcRCT) study design**. Overall, there are 30 clusters participating, 10 clusters in each state, and so the above figure shows the design that is replicated in each state. In each cluster, we aim to recruit 10 study participants having dementia or cognitive impairment, making the overall recruitment target at 300 participants. Data are collected from all participants during the seven data collection time points shown by a dashed-line in the above figure (i.e., at baseline and 3, 6, 12, 15, 18, and 24 months). We expect an attrition rate of 20 percent; therefore, we expect approximately 240 participants with dementia or cognitive impairment and approximately 1,680 participant data points to be examined in this SWcRCT. Attrition is expected to occur at any time point, and the modeling will include all participant data; participant data may be complete (available from all seven time points) or incomplete (available from one to six time points). The intensive intervention phase is shown in dark blue. The post-intervention phase is shown in light-blue (this is the second year for the year 1 intervention group), where participants can still access the intervention, but the intervention will no longer be promoted at those clusters.

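### The imputation prescribed for both primary outcomes leaves out intervention status and cluster, so an imputed analysis would pull the estimated effect towards zero

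*Protocol article*

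**What the plan says.** The Missing Data section of the protocol article begins: "The analysis method chosen will use all available data". It then prescribes imputation "for each primary outcome and other key variables with missing data", whatever the missing-data analysis shows about data missing not at random. The method is "multiple imputation using multivariate regression with factors of age, gender, state, and time will produce 100 estimates for each missing item".

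The analysis model is given under Primary Analyses: "The model will include intervention status and time as fixed effects and cluster site and individuals as random effects". Time is the only term that both models are certain to share. Intervention status, cluster and individual are in the analysis model but not in the imputation list, and no other section adds them.

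On the amount of missing data, the Figure 1 legend says "We expect an attrition rate of 20 percent" and "Attrition is expected to occur at any time point, and the modeling will include all participant data". The Missing Data section ends: "A detailed analysis plan will be developed for secondary and sensitivity analyses".

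**The concern.** An imputation model should contain at least the terms of the analysis it feeds, above all the one being estimated. Here the imputed QOL-AD and CES scores of the two groups are drawn around the same mean at each visit. At visits where one group has the intervention and the other does not, this moves the groups together. Drawing 100 values per missing item reduces simulation noise but does not remove this bias.

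Without cluster and the person's other scores, the imputed values also carry too little of the correlation that the mixed model relies on. That inflates the residual variance and the standard error.

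The trial is powered at 0.80 for effects of 0.23 to 0.25 SD, so avoidable shrinkage and added noise both work against finding a real benefit.

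**Working it through.** **Inputs from the protocol article.** 30 clusters of 10; half start in year 1 and half in year 2; seven visits (baseline, 3, 6, 12, 15, 18, 24 months); ICC 0.05; QOL-AD SD 7; effect 0.23 SD; power 0.80; significance level 0.05; attrition 20%.

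**Assumptions.** Two-sided test. Group A counts as intervention from month 3 (0111111) and Group B from month 15 (0000111). Total within-person correlation is 0.5 or 0.7. Dropout is unrelated to the scores.

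**1. The plan's own figures.** 300 × 0.8 = 240 and 240 × 7 = 1,680, as stated. The stepped-wedge (Hussey-Hughes) variance is

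Var = Iσ²(σ² + Tτ²) / [(IU − W)σ² + (U² + ITU − TW − IV)τ²],

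with I = 30, T = 7, U = 135, W = 3,375, V = 675 and τ² = 0.05.

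- 10 per cluster: σ² = 0.95/10 = 0.095. Var = 1.26825/199.125 = 0.00637, SE 0.0798. The detectable effect is 0.224, and power at 0.23 is 0.822.
- 8 per cluster: σ² = 0.11875. Var = 1.6699/215.156 = 0.00776, SE 0.0881. The detectable effect is 0.247; power is 0.810 at 0.25 and 0.742 at 0.23.

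The design is therefore reproduced approximately. The point below does not depend on it.

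**2. Expected shrinkage.** Let a share m of scores be missing at a visit in both groups. If imputed scores share one mean, a true group difference δ becomes (1 − m)δ. Under the layout above, the groups differ in status only at months 3, 6 and 12.

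- Dropout of 20% spread evenly over the six follow-up visits gives m = 0.2 × 1/6, 0.2 × 2/6 and 0.2 × 3/6, that is 0.033, 0.067 and 0.100. The mean is 0.067, so about 0.93 of the effect remains.
- With 20% missing at every follow-up visit, 0.80 remains.

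**3. Simulation.** 30 × 10 × 7 data, pooled by Rubin's rules and fitted with random cluster and person intercepts; 300 replicates with 10 imputations each. Entries are mean estimate divided by true effect.

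| Within-person r | Dropout of 20% | Missing at 3–12 months | Listed factors | Plus intervention status | Joint over visits, no group | Joint plus group |
|---|---|---|---|---|---|---|
| 0.5 | spread | 6.7% | 0.950 | 1.019 | 0.916 | 1.009 |
| 0.5 | before month 3 | 20.0% | 0.795 | 0.991 | 0.786 | 0.990 |
| 0.7 | spread | 6.8% | 0.934 | 1.007 | 0.891 | 0.989 |
| 0.7 | before month 3 | 19.8% | 0.809 | 1.006 | 0.806 | 1.004 |

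The listed factors behave as step 2 predicts, and adding status or group removes the bias. With intermittent missingness also run (150 replicates), the listed factors kept 0.79 to 0.82 of the effect when 20% of the 3–24 month scores were missing. The mixed model on available data gave 0.97 to 1.03 without imputation.

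**4. Correlation.** In the four runs, the listed factors lowered within-person correlation from 0.50 to 0.43 and 0.40, and from 0.70 to 0.60 and 0.56. With intermittent missingness it reached 0.35 and 0.48. Cluster ICC fell from 0.053–0.056 to 0.039–0.046. Adding status alone did not repair this (0.43 and 0.40 against 0.50). Joint imputation kept within-person correlation at 0.50 and 0.70.

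**5. Power.** At r = 0.5 with dropout before month 3, power was 0.97 on complete data, 0.72 with the listed factors and 0.91 with joint imputation plus group. So the drop from 0.97 to 0.91 remains even with the fuller imputation model, and the drop from 0.91 to 0.72 comes from the listed one. The mean SE rose from 0.425 to 0.529. With spread dropout the three powers were 0.97, 0.90 and 0.96. These exceed the planned 0.80 because the assumed within-person correlation adds precision.

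**6. In points.** 0.23 × 7 = 1.61 QOL-AD points. A loss of 5 to 7% is 0.08 to 0.11 points; 20% is 0.32 points.

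**The case against.** The strongest reply is that the imputed fit may not be the primary result. The Missing Data section, Primary Analyses and the Figure 1 legend all say that all data, complete or not, enter the modelling, which suits a mixed model on observed records. This stands. A reader might infer that the trial's primary estimate is known to be biased, but the text does not establish that. It does prescribe imputation for each primary outcome and gives it no role, so two estimates could each be called primary.

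Four other stronger readings are tempting and go too far:

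- **Every missing score is imputed as if there were no effect.** With the coding above, the groups share the same status at baseline and at 15, 18 and 24 months. Under the model's constant effect, time then already carries status at those visits.
- **Within-person correlation is certainly lost.** Multivariate regression may mean joint imputation of all seven scores, which keeps it. Listing time as a factor points the other way, but the wording is open. The shrinkage survives either reading (0.79 to 0.92 of the effect under the joint one).
- **Data missing not at random are ignored.** The same section plans sensitivity analyses of the missing-data assumption.
- **The protocol expects waiting to raise dropout.** The Strengths and Limitations section says only that it may.

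It is also fair that the bias is modest when dropout is spread, the pattern closest to the Figure 1 legend, and that it runs towards zero and so does not create a false benefit.

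The reply that the four factors are shorthand, or left to a later plan, is weaker. Primary Analyses names intervention status as a factor in another multivariate analysis, and the later plan is promised only for secondary and sensitivity analyses.

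**Conclusion.** The point holds and should be fixed. As written, the imputation model omits intervention status and cluster, and any fit to data imputed this way underestimates the effect: by roughly 5 to 7% with 20% dropout spread over follow-up, and up to about 20% if 20% of follow-up scores are missing. If the seven scores are imputed jointly without group, the loss with spread dropout is 8 to 11%. Cluster correlation is diluted, and within-person correlation too unless imputation is joint.

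The direction follows from the omission itself. The sizes rest on the assumed missingness patterns, within-person correlations of 0.5 and 0.7, dropout unrelated to the scores, and Group A counted as intervention throughout year 2. The documents give none of these beyond the 20% attrition. Whether the bias reaches the reported primary result depends on which fit is primary, and the text leaves that unsaid.

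**What to change.** State that the linear mixed model on all observed waves is the primary analysis for QOL-AD and CES. It already uses incomplete records and is valid under missing at random. Give multiple imputation an explicit role as a sensitivity analysis, if it is kept. Its model should then include intervention status (or group by wave), cluster and the person's other scores alongside the listed factors, in a multilevel or joint form compatible with the analysis model. Say which form multivariate regression refers to.

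The cost is analysis wording and code only. Recruitment, visits and data collection do not change.
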